#### Definition of covariates

Potentially associated factors of frailty in the models included [16, 36–43] age, sex, ethnicity, education level, marital status, body mass index (BMI), living alone, living conditions, smoking, alcohol consumption, falling accidents in the past 12 months, immobilization for more than 4 weeks, polypharmacy, fatigue, resistance (ability to climb stairs), ambulation (ability to walk 100 m), illnesses (> 5), loss of more than 5 % body weight, nutritional risk, ADL, instrumental ADL, depression, cognitive function, handgrip strength, vision, hearing, sleeping, urinary function, and defecation function.

Age was grouped as 65–74 years old, 75–85 years old, and 85 years old and above. Ethnicity was categorized as Han and ethnic minorities. Education level was categorized as illiterate, primary school, junior high school, and high school and above. Marital status was categorized as married and divorced or widowed. Living alone was categorized as living alone or not living alone [40]. Living conditions was classified as living in a building with an elevator, a building without an elevator, or a bungalow. Polypharmacy was categorized as 0, 1–2, 3–4, 5–6, and more than 7 [16].

BMI was calculated as body weight divided by height (in meters) squared (kg/m^2^) [18] and was used to classify patients into groups of < 19 kg/m^2^, 19 to < 21 kg/m^2^, 21 to < 23 kg/m^2^, and ≥ 23 kg/m^2^. Participants’ weight in kg was measured to the nearest 0.1 kg using a digital electronic chair scale, and height (in cm) was measured to the nearest 1 mm using a stadiometer. Study participants were weighed while wearing light clothing and no shoes.

We referred to the FRAIL scale [38, 44], such as the items of fatigue, resistance (ability to climb stairs), ambulation (ability to walk 100 m), illnesses (> 5), and loss of more than 5 % body weight, which has been validated in Chinese older adults [45].

Nutritional risk was measured using the MNA-SF, a six-item scale with scores ranging from 0 to 14 points [19]. Patients were categorized into patients at risk of malnutrition (8–11 points) or malnourished (0–7 points) [39]. The MNA-SF has been validated in the Chinese population and has excellent test characteristics [10, 46].

ADL were measured using the Barthel Index, which is a 10-item instrument measuring disability in terms of a person’s level of functional independence in personal ADL [47–49]. A higher score means better capacity to perform daily living activities [48, 49]. Patients were categorized into those with a score < 75 and ≥ 75.

Instrumental ADL were measured using the Instrumental Activities of Daily Living Scale [50], which includes a range of higher-level activities that are considered to address the capacity of older adults to interact with their community [51]. The scores on this scale range from 0 to 8, with 0 being the least independent and 8 being the most independent [50, 52, 53]. Patients were categorized into groups with scores of < 6 and ≥ 6 on the eight-item scale.

The depression assessment scale was developed on the basis of the Geriatric Depression Scale 15 (GDS15) [54], with a higher score denoting more severe depression. Patients were categorized into groups with scores of 0–5 and 6–15.

Assessment of cognitive function was on the basis of the Mini-Cog [55, 56] and was dichotomized as normal cognitive function (scores of 3–5) and cognitive dysfunction (scores 0–2).

Handgrip strength was categorized as normal (greater than 28 kg in men and greater than 18 kg in women) and abnormal, according to the Asian Working Group for Sarcopenia in 2019 [57].

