### Developing the frailty model according to nutritional risk

#### Data used for modeling

The data used for development of the prediction model were derived from an ongoing, prospective large-scale cohort study among older Chinese inpatients at tertiary hospitals (Chinese Clinical Trial Registry Number: ChiCTR1800017682). In the present study, we used baseline survey data collected from October 2018 to February 2019; details can be found elsewhere [3, 10]. Briefly, this study is a nationwide survey that provides representative data for the investigation of geriatric factors, such as nutritional status, cognition, or physical activity, in hospitalized older individuals aged ≥ 65 years nationwide. Eligible participants are recruited from five provinces and one municipality in China (southwest: Sichuan Province; northeast: Heilongjiang Province; south–central: Hubei Province; northern: Beijing municipality/city; northwest: Qinghai Province; eastern: Zhejiang Province). All eligible older individuals are continuously enrolled. Surveys are administered by trained nurse interviewers using a structured questionnaire. The interview language used is standard Mandarin/Putonghua. Proxy respondents, usually a spouse or other legal guardian, are interviewed if the patient is unable to answer the questions themselves.

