#### Feasibility of recruitment and sample size

In the first stage, for the sample size required for modeling, we referred to the method of estimating sample size for multivariate logistic regression. For the categories with a smaller proportion of the outcome variables, the sample size should be at least 10 times the number of independent variables. There are two categories of dependent variables in this study (no frailty and frailty), and 20 important independent variables were initially estimated. Therefore, the sample size of the intervention group in this study is at least 200 patients. According to the literature data, the incidence of frailty in the older population with nutritional risk is approximately 26.5–54 % [18, 32, 34, 35]. Taking into account an expected incidence of 40 % and loss to follow-up of 10–20 %, we aim to include 600 patients. As for the total sample size, with reference to logistic regression modeling requirements, the modeling sample size is approximately two-thirds of the total sample size and the model verification sample size is approximately one-third of the total sample size. The total sample size is calculated to be at least 900 patients, of which at least 300 patients will be used for model verification.

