#### Population and inclusion and exclusion criteria

In the first stage of modeling, participants must meet the following criteria: having no frailty according to the FRAIL (Fatigue, Resistance, Ambulation, Illnesses, & Loss of Weight) scale (scores from 0 to 2), malnourished or at risk of malnutrition according to the Mini-Nutritional Assessment-Short Form (MNA-SF; scores range from 0 to 11), and written informed consent provided by patients enrolled in this study.

Exclusion criterion were as follows: patients with frailty at the time of enrollment; patients who are persistently unconsciousness or unable to provide informed consent for participation, or their caregivers were unable to provide effective information; patients who were initially admitted to the intensive care unit (ICU) [13]; patients with anorexia nervosa, acute pancreatitis, acute liver failure, cystic fibrosis, stem cell transplantation, severe chronic gastrointestinal diseases, acute infectious diseases or chronic wasting diseases at enrollment; and patients who were lost to follow-up or had died at the 30-day of follow-up. A total of 3027 patients were enrolled in the current study.

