#### Outcomes

The dependent (outcome) variable is frailty, defined as “multi-systemic functional decline below a certain level, leading to increased vulnerability to a minor stressor with poor outcomes of disability and/or mortality” [16, 58]. The outcome will be expressed using three categories: non-frail, pre-frail, and frail when meeting 0, 1 or 2, and ≥ 3 criteria of the FRAIL scale. A larger total score indicates more a severely frail condition.

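### Stage 1 does not fix when the frailty outcome is measured, and its total AUC cannot show what the model adds to the baseline FRAIL score

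*Protocol article*

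**What the plan says.** All references are to the stage 1 part of the protocol article.

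- **Data used for modeling:** "we used baseline survey data collected from October 2018 to February 2019".
- **Population and inclusion and exclusion criteria:** entry requires "having no frailty according to the FRAIL (Fatigue, Resistance, Ambulation, Illnesses, & Loss of Weight) scale (scores from 0 to 2"). Exclusions include "patients with frailty at the time of enrollment" and "patients who were lost to follow-up or had died at the 30-day of follow-up".
- **Definition of covariates:** the candidate predictors include "fatigue, resistance (ability to climb stairs), ambulation (ability to walk 100 m), illnesses" and weight loss. The section names the FRAIL scale as their source.
- **Outcomes:** "The outcome will be expressed using three categories: non-frail, pre-frail, and frail", with frail meaning three or more FRAIL criteria. No assessment time is given.
- **Feasibility of recruitment and sample size:** "There are two categories of dependent variables in this study (no frailty and frailty"). The calculation uses an expected incidence of 40 % and a loss to follow-up of 10–20 %.
- **Statistical considerations:** predictors are selected by logistic regression at P < 0.05. The model is judged by AUC and the Hosmer–Lemeshow test, with accuracy and AUC in the verification set.

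**The concern.** Outcome and predictors come from the same five-item scale, and the plan does not clearly separate them in time. Two things follow.

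First, the dependent variable of stage 1 is not defined consistently. One section points to baseline data, the entry criteria remove every patient who could be a baseline case, and the section that should settle the matter gives no time. The number of outcome levels also differs between sections.

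Second, even with a later outcome, a patient who enters with two positive items needs only one more to become frail if those two persist. A model that contains the baseline items will discriminate for that reason alone. The study's stated gap is the degree to which nutritional risk influences frailty (Background), and its promised product is a tool focused on nutrition, cognition and depression (Discussion). A total AUC does not separate those contributions from the baseline score, and the model is then taken into stage 2 for screening.

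**Working it through.** **1. The plan's own sample size.** Events = 10 × 20 predictors = 200. N = 200 / 0.40 = 500. Allowing for loss, 500 / (1 − 0.10) = 556 and 500 / (1 − 0.20) = 625; the planned 600 lies between them (it is also 500 × 1.20). Total = 600 / (2/3) = 900. The figure reproduces. Its inputs, incidence and loss to follow-up, make sense only if frailty is assessed after entry.

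**2. Events under each outcome time.**

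| Outcome time | Consequence |
|---|---|
| Baseline, with the entry criteria | Highest possible FRAIL score is 2: 0 events against 200 required |
| Baseline, ignoring the entry criteria | Items sum to the outcome score: AUC = 1.0. The entry criteria rule this out |
| Day 30, FRAIL 0–2 at entry | Events can occur; consistent with the 30-day exclusions, the incidence and the loss allowance |

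Only the third row gives a model that can be fitted and that fits the rest of the plan.

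**3. Carry-over on the day-30 reading.** The documents give no item-level rates, so every rate here is an assumption. Take five independent items with baseline prevalences 0.45, 0.30, 0.25, 0.15 and 0.30, restricted to a sum of 0–2. The shares with score 0, 1 and 2 are then 0.201, 0.438 and 0.361. Let a positive item persist with probability q and a negative one become positive with probability p, with no effect of any other predictor. For baseline score k:

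day-30 score = Bin(k, q) + Bin(5 − k, p), and risk_k = P(score ≥ 3).

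AUC = Σ_k P(k | event) × [P(j < k | no event) + ½ P(j = k | no event)].

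For q = 0.9 and p = 0.10:

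- The risks are 0.0086, 0.0474 and 0.2246.
- Incidence = 0.201 × 0.0086 + 0.438 × 0.0474 + 0.361 × 0.2246 ≈ 0.104.
- The score shares are 0.017, 0.201 and 0.783 among events, and 0.222, 0.466 and 0.312 among non-events.
- AUC = 0.017 × 0.111 + 0.201 × (0.222 + 0.233) + 0.783 × (0.688 + 0.156) ≈ 0.754.

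Exact enumeration gives:

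| q | p | Day-30 incidence | Item-only AUC |
|---|---|---|---|
| 0.9 | 0.10 | 10.4 % | 0.754 |
| 0.8 | 0.15 | 14.1 % | 0.710 |
| 0.7 | 0.20 | 17.3 % | 0.663 |
| 0.9 | 0.30 | 38.0 % | 0.676 |
| 0.8 | 0.35 | 41.2 % | 0.633 |
| 0.7 | 0.30 | 30.0 % | 0.621 |
| 0.7 | 0.40 | 44.2 % | 0.588 |
| 0.5 | 0.20 | 12.1 % | 0.613 |
| 0.5 | 0.40 | 35.8 % | 0.530 |

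For persistence of 0.7–0.9, the AUC is about 0.59–0.75. At incidences of 30–44 %, nearer the plan's 40 %, it is about 0.59–0.68. If items persist poorly, the effect nearly vanishes.

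**4. With another predictor present.** A separate simulation used 200,000 subjects before the restriction to FRAIL 0–2, correlated items, one other predictor, persistence of 0.5–0.95 and an onset parameter of 0.1–0.4. It gave incidences of 5–30 %. AUC was 0.67–0.71 without the baseline items and 0.70–0.85 with them. The gain ranged from 0.035 (0.669 to 0.704) to 0.143 (0.710 to 0.853), again depending on the assumed rates.

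**The case against.** The strongest reply is that the design is plainly one of incident frailty. The source is a prospective cohort, patients already frail are excluded, those lost or dead at 30 days are excluded, and the sample size speaks of incidence. This stands. A reader might infer that stage 1 will have no events among its 3027 patients. The documents do not support that as a forecast; it follows only if the baseline wording is taken alone.

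The second reply is that baseline components of a scale, measured before the outcome in patients below the cut-off, are admissible predictors. This also stands. A reader might infer that the AUC is inflated by leakage. On the day-30 reading it is not: a higher risk in patients entering with two positive items is real predictive information, and useful for screening.

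Third, the item-only calculation sets all other effects to zero, so it cannot show what share of a full model's AUC the items supply. Correct. With one other predictor of onset at an assumed log-odds of 1 per SD and incidence near 40 %, that predictor alone gave 0.79–0.80, the full model gave 0.81–0.85, and the items added only 0.01–0.06. The claim that the AUC would mostly reflect FRAIL predicting itself is therefore unsupported.

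Fourth, the entry criterion defines no frailty as 0–2, so merging non-frail and pre-frail recovers the two categories in the sample size. That is the natural reconciliation, but the Outcomes section does not make it.

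What survives is that the outcome time is unstated and conflicts with the data description, and that the planned measures cannot attribute the AUC.

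**Conclusion.** The point holds in limited form. The stage 1 text contradicts itself on its dependent variable: baseline data and an untimed outcome on one side, entry restricted to FRAIL 0–2 and 30-day follow-up on the other. The number of outcome levels also needs aligning. The day-30 reading is an inference from the exclusions and the sample size, since neither the data description nor the outcome definition states it.

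On that reading the AUC is valid as a measure of prediction, but part of it is carry-over of the baseline score. The size of that part is unknown. Items alone reach about 0.59–0.75 under the assumed rates, and less if items change quickly. The total AUC, Hosmer–Lemeshow test and accuracy therefore cannot establish what nutritional risk, cognition, depression or ADL add, which is what the study sets out to show. The conclusion does not depend on any one assumed rate, because the plan contains no comparison that would separate the two sources.

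**What to change.** 1. In Data used for modeling and in Outcomes, state that predictors are baseline values and that the outcome is binary, FRAIL ≥3 against 0–2, at the 30-day assessment. Align the stage 1 sample-size section with this, and keep the three-level grading as description only.
2. In Statistical considerations, add a reference model with the baseline FRAIL score alone. Report the AUC difference and the calibration of the full model against it, in the bootstrap and in the verification set, alongside the total AUC.
3. Dropping the five items is optional, for example as a sensitivity model. Removing them outright is a trade-off, because it discards legitimate predictors from a tool meant for screening.

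The cost is wording plus one extra model on existing data, provided FRAIL was recorded at 30 days as the exclusions imply. The model's added value may look smaller than the total AUC suggests.

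### Age bands overlap at 85 and drug-count bands omit 7; separately, cutting numeric predictors into groups discards information and makes the Barthel predictor constant in Stage 2

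*Protocol article*

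**What the plan says.** All of the predictor definitions are in the protocol article under Definition of covariates, in the part on developing the frailty model.

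- Age: "Age was grouped as 65–74 years old, 75–85 years old, and 85 years old and above".
- Number of drugs: "Polypharmacy was categorized as 0, 1–2, 3–4, 5–6, and more than 7".
- BMI, from weight measured to 0.1 kg and height to 1 mm, "was used to classify patients into groups of < 19 kg/m^2", then 19 to under 21, 21 to under 23, and 23 or more.
- MNA-SF: "Patients were categorized into patients at risk of malnutrition (8–11 points) or malnourished (0–7 points").
- Barthel Index: "Patients were categorized into those with a score < 75 and ≥ 75".
- Instrumental ADL: "Patients were categorized into groups with scores of < 6 and ≥ 6 on the eight-item scale".
- GDS-15: "Patients were categorized into groups with scores of 0–5 and 6–15".
- Mini-Cog is split at 0–2 against 3–5, and grip strength at 28 kg for men and 18 kg for women.

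For Stage 2, the section on population and inclusion and exclusion criteria requires age 65 or more and a Barthel score of at least 75. The Procedure section gives the Barthel range as 0 to 100. No section resolves the age or drug bands, and none says that the numeric form of any of these measures will enter the model.

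**The concern.** There are two separate problems.

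The first is definitional. A prediction model has to give each patient one value per predictor. As printed, age does not do so at 85 and drug count does not do so at 7. Two analysts following the text could code the same patients differently, and so could two users of the resulting tool if these predictors are retained.

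The second is a modelling choice. A banded predictor treats everyone within a band as having the same risk and makes risk jump at each cut. Ages 65 and 74 are treated alike, as are GDS-15 scores of 6 and 15. For measures already recorded as numbers, this gives up predictive information without saving any data collection. It matters most where the band boundary coincides with an eligibility limit, because the predictor then carries no information at all in the patients to whom the model is applied.

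**Working it through.** **1. Do the bands cover every value exactly once?** For each measure, count how many stated groups contain each possible value.

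| Measure | Groups as stated | Values not in exactly one group |
|---|---|---|
| Age (65 and over, no upper limit stated) | 65–74; 75–85; 85 and above | 85 is in two |
| Number of drugs | 0; 1–2; 3–4; 5–6; more than 7 | 7 is in none |
| BMI | under 19; 19 to under 21; 21 to under 23; 23 or more | none |
| MNA-SF (eligible range 0–11) | 0–7; 8–11 | none |
| Barthel | under 75; 75 or more | none |
| Instrumental ADL (0–8) | under 6; 6 or more | none |
| GDS-15 | 0–5; 6–15 | none |
| Mini-Cog | 0–2; 3–5 | none |
| Grip strength | above the sex-specific cut; otherwise abnormal | none |

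The fault is confined to age and drug count among the numeric measures. Either 75–84 with 85 and over, or 75–85 with 86 and over, removes the age overlap; the document does not show which was meant. Starting the top drug band at 7 closes the gap. Among the non-numeric predictors, marital status ("Marital status was categorized as married and divorced or widowed") likewise names no group for never-married patients.

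**2. Barthel in Stage 2.** The predictor equals one value for scores of 75 or more and another below. Stage 2 admits only scores of 75 or more. Every Stage 2 patient is therefore in the same group and, if the predictor is retained, it adds the same amount to everyone's score. In numeric form, scores from 75 to 100 could still differ between patients.

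**3. Size of the information loss (illustration).** The document gives no distributions, so assume a normally distributed predictor with a linear effect. The share kept is the between-group variance over the total variance. For a split into proportions p and 1 − p at the standard normal quantile z, this is φ(z)² / [p(1 − p)]. At the median, φ(0)² / 0.25 = (1/2π) / 0.25 = 2/π = 0.637.

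| Grouping | Share kept |
|---|---|
| Two groups, 50/50 | 64% |
| Two groups, 30/70 | 58% |
| Two groups, 20/80 | 49% |
| Two groups, 10/90 | 34% |
| Three equal groups | 79% |
| Four equal groups | 86% |

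**4. Parameters.** A predictor in g groups uses g − 1 parameters.

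- As banded: age 3 − 1 = 2, BMI 4 − 1 = 3, drug count 5 − 1 = 4; total 9.
- As continuous terms: a 3-knot restricted cubic spline uses 2 parameters, so age 2, BMI 2, drug count (linear) 1; total 5.
- Each measure cut in two uses 1 parameter, and so does its linear term, so nothing is saved there.

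**The case against.** The overlap and the gap may be slips of wording. The article describes data already collected, and the working codebook, which is not shown, may be correct. That is plausible, but the published definition is what a reader or user would apply, and nothing in the document corrects it.

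Several cuts carry citations, and a bedside screening tool benefits from simple bands. The first-stage section on population reports 3027 enrolled against a stated need of at least 900, which weakens an argument from efficiency. The bivariate tests in Statistical considerations also include methods for quantitative variables, so bands are not the only form used. These points temper the concern without removing it: a simple chart can be derived after a continuous fit, and a large sample does not restore variation to a Barthel predictor that is constant in Stage 2.

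A reader might infer more than the document supports:

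- **That the predictor bands are faulty in general.** Among the numeric measures, only age and drug count are, and an 85-year-old can be coded, though not uniquely.
- **That patients on 7 drugs would be dropped from the model.** No complete-case rule is stated.
- **That the faulty bands must be used at the bedside.** Predictors are selected at P < 0.05, so age or drug count might not be retained.
- **That calibration will suffer.** A grouped model can be calibrated within its groups.
- **That about a third of the information is lost throughout.** The 36% loss (100 − 64) belongs to a median split of a normal predictor. Age, BMI and drug count have three or more groups, and several of the scores are short ordinal scales.

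**Conclusion.** The point holds in two parts. As printed, age 85 has no unique code and 7 drugs has no code; this follows from the text and needs no assumption. The number of patients affected cannot be computed, because the age and drug-count distributions are not given.

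Separately, the article fixes eight numeric measures as two to four groups each, which discards predictive information. The one consequence demonstrable from the document is that the Barthel predictor, if retained, cannot separate any Stage 2 patient. Otherwise the size of the loss in this cohort is unknown; the percentages above rest on normality and a linear effect and are illustrative. The saving of 4 parameters (9 − 5) applies to age, BMI and drug count only, and assumes that a raw drug count was recorded.

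This bears on reproducibility and on how well the model performs. It does not invalidate the study.

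**What to change.** - Make the age and drug-count bands exclusive and exhaustive wherever bands are kept. The investigators should state which age boundary was meant and give 7 drugs a group. A group for never-married patients can be added in the same correction.
- Fit the model with age, BMI, MNA-SF, Barthel, instrumental ADL, GDS-15, Mini-Cog and grip strength as continuous terms, for example with 3-knot restricted cubic splines for age and BMI, and grip strength entered with sex. Enter drug count as a number if a raw count was recorded; if only the bands were collected, use the corrected bands.
- Derive any bedside points chart after fitting, from the continuous model.

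For measures held as raw values this is a coding change with no new data collection. The downside is that a points chart or calculator replaces simple bands in clinical use.
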